### Method of blinding

Trial participants and investigators will be blinded to treatment allocation. Site pharmacies and other authorised delegates as required will be unblinded. Treatment products/pre-medication and the corresponding control will have identical presentations in product appearance, packaging and labelling.

### Primary outcome

The primary outcome is the time to start of symptomatic recovery. Symptomatic recovery is defined as symptomatic remission sustained for at least 6 months [21]. Symptomatic remission is defined as a score of 3 or less on each of the following PANSS [18] items: P1, P2, P3, N1, N4, N6, G5 and G9.

### Secondary outcomes

Time to symptomatic remission

Symptomatic remission is defined as a score of 3 or less on each of the PANSS items P1, P2, P3, N1, N4, N6, G5 and G9, regardless of whether or not this response is sustained for 6 months (i.e. response, but does not reach the duration criterion for recovery).2.Relapse

Relapse outcome is defined as the proportion of participants who relapse at least once during the 12-month follow-up period. Relapse is defined as a score of 4 or more on at least one of the PANSS items P1, P2, P3, N1, N4, N6, G5 or G9 after initial symptomatic remission occurred during the 12-month follow-up period.3.Number of adverse events (AEs) over the 12-month follow-up period

The total number of AEs, total number of serious adverse events (SAEs) and total number of AEs with grade III or IV as reported in the AE CRF over the 12-month follow-up period will be presented by randomised group.4.Number of serious infections

The total number of reported serious infections and the number of serious infections per participant over the 12-month follow-up period will be reported for each randomised group.5.Proportion of patients reaching 20%, 30% and 40% reduction in PANSS total score over the 12-month follow-up period.

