### Participants

#### Inclusion criteria

Age 18–70 years.Acute psychosis symptoms for at least 2 weeks but not longer than 24 months in the current episode. Acute psychosis is defined as rating 4 or more for at least one of the following Positive and Negative Syndrome Scale (PANSS) [18] items: P1, delusions; P2, conceptual disorganisation; P3, hallucinatory behaviour; N1, blunted affect; N4, social withdrawal; N6, lack of spontaneity; G5, mannerisms/posturing; and G9, unusual thought content. This may be either a first episode or relapse after remission. Remission is defined as having mild or absent symptoms of psychosis for at least 6 months.Serum or cerebrospinal fluid (CSF) anti-neuronal membrane antibodies at pathological levels (including NMDAR, LGI1 and others, as determined by the Trial Steering Committee).Given informed consent by a patient or their legal representative.

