### Sample size

To estimate the control rate for the primary outcome efficacy measure, we have re-analysed the raw data of the National EDEN study [27]. This study consisted of 1000 patients with psychosis (antibody associations not known); 19% of those, who were symptomatic at entry, experienced sustained remission as per the Andreasen et al. criteria [21] on standard antipsychotic therapy at 1 year. The 50% remission rate on immunotherapy that we have selected is a conservative estimate; in anti-NMDAR encephalopathy, remission may be as high as 85% at 1 year following IVIG and rituximab [7]. We agreed on 50% as a clinically meaningful and important remission rate that from a patient perspective would make participation in the trial acceptable. The Trial Steering Committee (TSC) and statistician will analyse recruitment and dropout rates at months 12 and 24 of the trial, and consider altering the recruitment strategy. We have chosen a sample size to target a time-to-remission hazard ratio of 0.322 with a one-sided type I error rate of 5% and a power of 80%, standard for a stage II clinical trial. This target hazard ratio comes from assuming a 1-year remission probability of 0.2 in the control arm and 0.5 in the experimental arm and assuming the time-to-remission distribution is exponential with proportional hazards. With all participants followed up for 1 year, a sample size of 56 participants equally randomised between the control and experimental arms is required. The sample size was calculated using NCSS PASS v14. We intend to recruit about 80 participants, allowing dropout of 12 participants per arm. This level of dropout is a cautious estimate because, although a high dropout is often seen in drug trials in psychosis, we are not requiring continued compliance with medication regimes after the infusions of IVIG and rituximab.

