### Statistical analysis methods

The final analysis will use a Cox proportional hazards model with fixed effects for minimisation covariates. The primary analysis will be per protocol rather than intention to treat, although both will be done. Secondary and exploratory outcomes will be analysed with Cox models (time to any remission), logistic regression models (relapse rate, proportion of participants with serious adverse events) and Poisson models (number of adverse events). The per-protocol population is defined as all participants who have received all protocol-defined IMPs, and have no major protocol violation as defined prior to analysis. A full detailed analysis plan will be prepared by a statistician who is independent from the study.

Data on trial progress such as recruitment and participant dropout at months 12, 24 and 36 of the trial (after activation of the first site) and quality of data will be reported to both the Trial Steering Committee and the Data Monitoring Committee (DMC). The Trial Steering Committee will consider opening additional sites and/or modifying eligibility criteria if recruitment rates are below those expected. There will be no interim analyses of efficacy.

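### The relapse outcome scores participants who never remit as free of relapse, so its between-arm comparison mixes reaching remission with keeping it

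*Protocol article*

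**What the plan says.** All references are to the protocol article.

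- **Secondary outcomes, item 2**, sets the measure: "Relapse outcome is defined as the proportion of participants who relapse at least once during the 12-month follow-up period". The event is a score of 4 or more on at least one of the eight PANSS items, counted only "after initial symptomatic remission occurred during the 12-month follow-up period".
- **Secondary outcomes, item 1**, defines remission for this purpose without any duration requirement.
- **Inclusion criteria** make every participant symptomatic on the same eight items at entry: "Acute psychosis is defined as rating 4 or more for at least one of the following Positive and Negative Syndrome Scale (PANSS" items listed there.
- **Statistical analysis methods** name the model: "logistic regression models (relapse rate, proportion of participants with serious adverse events".
- **Sample size** gives the only remission rates in the article: "assuming a 1-year remission probability of 0.2 in the control arm and 0.5 in the experimental arm". The control figure is drawn from an earlier cohort in which 19% had sustained remission at one year.

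The article does not restrict the denominator to participants who remitted, does not allow for time at risk, and does not count failure to remit as an unfavourable result.

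**The concern.** Nobody is at risk of relapse at randomisation. A participant enters the risk set only by remitting, and remission is what the treatment is meant to bring about. The outcome therefore takes its best value, no relapse, for two opposite courses: remission that lasts, and illness that never remits.

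The 12-month window adds to this, because a participant who remits earlier has longer in which to relapse.

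The result could mislead in either direction. A treatment that brings more people into remission may show a higher relapse proportion for that reason alone. A real benefit in keeping people well may be cancelled or hidden. The secondary result could then appear to contradict the primary one without any true conflict. The article fixes both the definition and the model, so this is more than a detail left to the analysis plan.

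**Working it through.** **Step 1: the plan's own figures.** The inputs are in the Sample size section: one-year probabilities 0.2 and 0.5, one-sided 5%, power 80%.

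- Hazard ratio: ln(0.8)/ln(0.5) = 0.322, as stated.
- Schoenfeld events: 4 × (1.645 + 0.842)² / (ln 0.322)² = 19.25.
- Participants: 19.25 / 0.35 (the mean of 0.2 and 0.5) = 55.0, or 56 in equal arms, as stated.

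The design rates are coherent. The article gives no expected rate and no power for relapse.

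**Step 2: decomposition.** In each arm, P(relapse) = P(any remission) × P(relapse given remission) = r × q. The logistic comparison sees only the product.

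**Step 3: equal relapse risk per remitter.** Take r = 0.5 v 0.2 as illustrative any-remission rates. The values of q are assumed.

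| q in both arms | Active | Control | Ratio | Odds ratio |
|---|---|---|---|---|
| 10% | 5% | 2% | 2.5 | 2.58 |
| 30% | 15% | 6% | 2.5 | 2.76 |
| 50% | 25% | 10% | 2.5 | 3.00 |

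The ratio is 0.5/0.2 = 2.5 whatever the value of q.

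**Step 4: break-even.** The two arms show equal proportions when q(active)/q(control) = r(control)/r(active).

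- r = 0.5 v 0.2: ratio 0.40. Active must cut relapse per remitter by more than 60% to look better.
- r = 0.7 v 0.4 (assumed): ratio 0.57, a cut of about 43%.
- r = 0.8 v 0.5 (assumed): ratio 0.625, a cut of about 37%.

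Example at 0.5 v 0.2 with relapse per remitter halved from 40% to 20%: the proportions are 0.5 × 0.20 = 10% v 0.2 × 0.40 = 8%, an odds ratio of 1.28 against active. Among remitters the odds ratio is (0.20/0.80)/(0.40/0.60) = 0.375 in favour of active.

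**Step 5: separating any from sustained remission.** Read 0.5 v 0.2 as sustained remission and assume any-remission of 0.7 v 0.4. If only those who fail to sustain remission relapse, the proportions are 0.7 − 0.5 = 20% and 0.4 − 0.2 = 20%, an odds ratio of 1.0. Relapse per remitter is then 0.2/0.7 = 29% v 0.2/0.4 = 50%, so a real advantage in keeping remission disappears. With any-remission of 0.7 v 0.6 (equally an assumption), the proportions are 20% v 40%, which favours active. This step ignores late relapses, dropout and relapses after month 12.

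**Step 6: time at risk.** Under the plan's exponential assumption, λ = −ln(1 − p), and the expected time after remission within one year is 1 − p/λ per randomised participant.

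- Control: 1 − 0.2/0.2231 = 0.104 years = 1.2 months.
- Active: 1 − 0.5/0.6931 = 0.279 years = 3.3 months, a ratio of 2.7.
- Per remitter: 3.34/0.5 = 6.7 v 1.24/0.2 = 6.2 months.

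At these rates most of the difference comes from how many remit. Earlier timing adds a little.

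**The case against.** The strongest objection concerns the base rate. The control figure of 0.2 derives from sustained remission, whereas relapse follows any remission. Applying a common relapse risk to 0.5 v 0.2 leaves out those who remit and fail to sustain it, who are the most obvious relapsers. A treatment expected to produce more sustained remission should also lower relapse per remitter, so equal risk is not a neutral default. This stands, and step 5 shows that it can remove the difference or reverse it.

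A reader might therefore infer too much from step 3: that the arm with more remissions is bound to look worse, or that the trial is likely to report significant harm. The article supports neither. The direction turns on rates it does not give. On significance, even at 20% v 8% (an assumed 40% risk in both arms) with 40 per arm, the usual two-proportion normal approximation gives about a 34% chance of two-sided p < 0.05.

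It can also be said that the denominator might be narrowed in the analysis plan, which is not shown. The wording as it stands has no such limit. Narrowing to remitters would compare groups formed after randomisation by an event that treatment affects.

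Lastly, relapse would be read beside the primary outcome and time to remission, both defined for everyone randomised, and the unconditional proportion is a legitimate description. That is fair, but neither of those outcomes captures loss of remission over the 12 months, which is what the relapse outcome is meant to measure.

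**Conclusion.** The point holds as a defect of definition. Never remitting is scored as a favourable result, and the logistic comparison cannot separate the effect on reaching remission from the effect on keeping it. The tendency is against an arm with more or earlier remissions.

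The size is not determined by the article. With 0.5 v 0.2 taken as any-remission rates and equal risk per remitter, the relapse proportion is 2.5 times higher on active, and a cut of more than 60% per remitter is needed to break even. With assumed any-remission of 0.7 v 0.4 the break-even cut is about 43%, and if only non-sustained remitters relapse the arms are level at about 20%. These are illustrations resting on assumed any-remission rates and relapse risks, not forecasts.

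The matter concerns one secondary outcome. The primary outcome and the sample size of 56 are unaffected.

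**What to change.** For the between-arm comparison, replace the relapse proportion with an outcome defined for every randomised participant. Two candidates are:

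- the proportion in remission without relapse at month 12; or
- the number of months in remission over the 12 months.

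Both credit reaching remission and keeping it, and both count never remitting as unfavourable. Both can be derived from data already scheduled: the Screening, baseline, treatment and follow-up section has clinical visits with PANSS every three months and researcher assessments of the primary outcome in the months between.

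Report relapse descriptively by arm, once among all participants and once among those who remitted, beside the remission results and without a between-arm test.

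The cost is a reworded secondary outcome and matching analysis text, with no new visits or data. The change should be made and dated before unblinding.

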### Primary outcome measure

The Positive and Negative Syndrome Scale (PANSS) [18] is a clinician/researcher-rated 30-item scale for the assessment of the severity of symptoms of schizophrenia based on information obtained from a patient during the interview and from their family members and clinicians. Each item is rated from 1 (absent) to 7 (extreme) and they are grouped into three subscales: Positive Scale, P (7 items); Negative Scale, N (7 items); and General Psychopathology Scale, G (16 items). The sum of individual ratings within each subscale gives score ranges of 7–49 for the Positive Scale and Negative Scale and of 16–112 for the General Pathology Scale. A higher score indicates severe symptoms.

The primary outcome will be assessed by eight selected PANSS items [21]. These include three Positive Scale items (P1, delusions; P2, conceptual disorganisation; P3, hallucinatory behaviour), three Negative Scale items (N1, blunted affect; N4, passive/apathetic social withdrawal; N6, lack of spontaneity) and two items from the General Pathology Scale (G5, mannerisms/posturing; G9, unusual thought content).

PANSS assessments will be conducted by trained researchers. Their training includes PANSS training by certified trainers followed by observed role-play interviews with feedback, observed mock interviews with non-patients and patients with psychosis, and mock-interview videoing and analysis. Thereafter, there will be periodical refresher training with certified PANSS trainers and researchers’ independent rating of individual patient video interviews over the trial period.

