The screening visit and assessments will usually be performed at the SINAPPS2 site local clinical research facility, but may also be performed at outpatient clinics. Informed signed consent will be obtained and this will be followed by screening assessments to establish eligibility. These will include physician review, physical examination, height and weight assessments, pregnancy test (urine sample) if appropriate, collection of demographic data and disease history, screening blood tests, monitoring blood tests, anti-neuronal membrane antibody assays, blood sample for future research, assessment of PANSS items P1, P2, P3, N1, N4, N6, G5 and G9, and concomitant medications.2.Baseline visit and assessments (Visit 2 (day 0, maximum 7 days before IVIG/placebo treatment))

The baseline visit will follow confirmation of a participant’s eligibility and randomisation. It will be arranged a maximum of 4 weeks after confirmation of eligibility. Participants will be reviewed by a physician for the period between screening and baseline dates. Clinical assessment (PANSS), assessment of adverse events and concomitant medication will be administered by a researcher.3.IVIG or placebo treatment (Visit 3 (days 1–4))

The first treatment will follow the baseline visit (0–7 days after baseline) and will be given in an appropriate outpatient or inpatient setting, as determined by local practice and clinical need. Data on adverse events and concomitant medication will be obtained.4.Rituximab or placebo 1 treatment (Visit 4 (day 28, + 7 days)

Rituximab or placebo first treatment will be given in an appropriate setting, as determined by local practice and clinical need. Anti-neuronal membrane antibody assays and a pregnancy test (a maximum of 7 days before the first dose of rituximab/placebo) will be taken and data on adverse events and concomitant medications will be recorded.5.Rituximab or placebo 2 treatment (Visit 5 (day 42, + 7 days)

Rituximab or placebo second treatment will take place 14 (+ 7) days after the rituximab first treatment and data on adverse events and concomitant medications will be collected.6.Follow-up clinical visits (months 3, 6 and 9 (12 and 15), ± 7 days)

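### The 20/30/40% PANSS response outcome takes a percentage of a total whose minimum is 30, so each level is stricter for milder participants and out of reach at low baselines

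*Protocol article*

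**What the plan says.** Under Secondary outcomes, item 5 is the "Proportion of patients reaching 20%, 30% and 40% reduction in PANSS total score over the 12-month follow-up period". The article gives no formula, does not mention the scale minimum, and does not name the assessment from which the reduction is measured.

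Under Primary outcome measure, PANSS "is a clinician/researcher-rated 30-item scale for the assessment of the severity of symptoms of schizophrenia". On scoring, "Each item is rated from 1 (absent) to 7 (extreme"), and the section gives "score ranges of 7–49 for the Positive Scale and Negative Scale and of 16–112 for the General Pathology Scale".

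Under Inclusion criteria, "Acute psychosis is defined as rating 4 or more for at least one of the following" eight PANSS items. No minimum total is required. The Outline of visits has screening rate only those items ("assessment of PANSS items P1, P2, P3, N1, N4, N6, G5 and G9, and concomitant medications"), while at Visit 2 the entry is simply "Clinical assessment (PANSS), assessment of adverse events and concomitant medication will be administered by a researcher".

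**The concern.** A percentage change has a stable meaning when zero on the scale means no symptoms. Here the symptom-free value is 30. Dividing the change by the whole total puts a fixed 30 points in the denominator that can never appear in the numerator. The lower the baseline, the larger the part of the total that is floor, and the larger the share of real symptoms that must go before a given percentage is met. Below some baseline, complete symptom loss is not enough.

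Two things are at stake. One is interpretation: the same label would mean partial improvement for one participant and complete loss of symptoms for another. The other is sensitivity: anyone whose baseline is too low for a level is a non-responder at that level whatever the treatment does, and so cannot contribute to a difference between arms.

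**Working it through.** **Inputs, all from the protocol article.** Thirty items scored 1 to 7, and the subscale sizes of 7, 7 and 16 items (Primary outcome measure); response levels of 20%, 30% and 40% of the total (Secondary outcomes, item 5); entry on one of eight items at 4 or more (Inclusion criteria).

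**Reproducing the stated ranges.** 7 × 1 = 7 to 7 × 7 = 49 for the Positive and Negative Scales; 16 × 1 = 16 to 16 × 7 = 112 for the General scale. These match the article. The total therefore runs from 7 + 7 + 16 = 30 to 49 + 49 + 112 = 210.

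**Lowest total consistent with entry.** One listed item at 4 and the other 29 at 1 gives 29 + 4 = 33. Because only eight items are rated at screening, no threshold on the total operates at entry.

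**Which baselines allow each level.** From baseline B the largest possible raw reduction is (B − 30)/B. A reduction of p is reachable only if B ≥ 30/(1 − p):
- 20%: 30/0.8 = 37.5, so 38 or more in whole points
- 30%: 30/0.7 = 42.9, so 43 or more
- 40%: 30/0.6 = 50, so 50 or more

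**How strict each level is.** The share of removable score that must go is p × B/(B − 30).

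| Baseline total | Removable points | Largest raw reduction | Share needed for 20% | for 30% | for 40% |
|---|---|---|---|---|---|
| 33 | 3 | 9.1% | unreachable | unreachable | unreachable |
| 47 | 17 | 36.2% | 55.3% | 82.9% | unreachable |
| 50 | 20 | 40.0% | 50% | 75% | 100% |
| 60 | 30 | 50.0% | 40% | 60% | 80% |
| 80 | 50 | 62.5% | 32% | 48% | 64% |
| 100 | 70 | 70.0% | 28.6% | 42.9% | 57.1% |
| 120 | 90 | 75.0% | 26.7% | 40% | 53.3% |

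**An eligible profile.** One listed item at 4, the other seven listed items at 3 and the remaining 22 at 1 totals 4 + 21 + 22 = 47. A 40% reduction needs 0.4 × 47 = 18.8 points, but only 17 can be lost. If this participant lost every symptom and stayed well for six months, the primary outcome would record recovery, while item 5 would record a non-response at 40%.

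**After subtracting the floor.** With (B − follow-up)/(B − 30), the maximum is 100% at every baseline above 30. The points needed for 20/30/40% are 14/21/28 at a baseline of 100, 6/9/12 at 60, 4/6/8 at 50 and 0.6/0.9/1.2 at 33. All are reachable. At 33, however, a one-point change is 1/3 = 33% and passes two of the three levels.

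**The case against.** The strongest objection is that the article never says the percentage is taken on the uncorrected total. It names a reduction in total score and promises a detailed analysis plan, which is not shown and which might subtract 30. That possibility is open. But the article does fix the quantity and the scale, and its wording taken literally gives the results above. This is a stated rule with a poor property, not merely an omitted detail.

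A second objection is that the very low totals may be rare. A total of 33 requires 29 of 30 items to be rated absent in someone with acute psychosis. This stands: the criteria allow such a person, but nothing shows that one will be enrolled. Three levels are also reported, so a participant who cannot reach 40% may still count at 20% or 30%.

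Third, the correction has its own weakness. For the lowest baselines it replaces unreachable levels with almost trivial ones. This also stands, and the fix has to deal with it.

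A reader might infer more than the document supports:
- **That the comparison is biased.** The floor applies equally in both randomised arms, so it does not favour either.
- **That the treatment difference is materially diluted, or easily upset by chance baseline imbalance.** Participants who cannot reach a level do lower the observable difference at that level, but without a baseline distribution the amount cannot be calculated. A stricter level that can still be reached need not shrink the difference.
- **That mild participants in general are counted as non-responders after full recovery.** This holds only below 38, 43 and 50 for the three levels.
- **That the outcome should be fixed at month 12.** The article states a 12-month window, and a single time point would change the outcome rather than clarify it.

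**Conclusion.** The concern holds in a limited form. As written, item 5 asks for a share of removable symptoms that rises as baseline falls: for the 40% level, 57% at a baseline of 100, 80% at 60 and 100% at 50. It sets levels that cannot be met below whole-point baselines of 38, 43 and 50. This rests on two readings: that the percentage is of the uncorrected total, and that the reduction is measured from baseline. It does not depend on any assumption about the treatment effect.

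How many participants fall in the affected range is unknown. The consequence is reduced sensitivity and a response label whose meaning varies with baseline, in one of five secondary outcomes. The primary outcome, time to remission and relapse all use item-level cut-offs and are unaffected, as is the sample size. The change is worth making because it costs little and uses data the trial already collects.

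**What to change.** Define percentage reduction in item 5 as (baseline total − follow-up total)/(baseline total − 30), and name the Visit 2 PANSS as baseline. This takes the Visit 2 assessment to be the full 30-item scale, since screening covers only eight items. Keep the stated 12-month window. Adjust the between-arm comparison for baseline PANSS total; severity is not among the minimisation factors, which are antibody type, illness duration and smoking. Report the raw percentage alongside.

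Add a rule for baselines at or near 30. The ratio is undefined at 30, and one point is already 33% at 33. Eligibility is judged at screening and Visit 2 may follow up to four weeks after it is confirmed, so a Visit 2 total below 33 cannot be excluded.

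The cost is a short change to the outcome definition and the rule for low baselines; no new data, visits or participants are needed. The downsides are the coarseness at very low baselines and corrected rates that are not directly comparable with studies using the raw percentage, which is the reason for reporting both.
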